### Data analyses

#### MRI data processing and analysis

##### Image preprocessing and brain segmentation for volumetric analysis

All MRI images will be processed using the following steps: (1) T2-weighted MR image of each subject will be linearly aligned onto their corresponding T1-weighted image; (2) brain extraction will be performed using a learning-based algorithm;^43^ (3) intensity inhomogeneity will be corrected;^44^ (4) T1- and T2-weighted images will be normalized to zero mean and unit variance; and (5) images will be segmented into white matter, cortical gray matter, lateral ventricle, external cerebrospinal fluid, and deep gray matter. Volumetric analysis will be conducted based on the segmented brain structures.^45,46^

##### Structural connectivity/DTI analysis

At each time point (0–1 month, 6 months, 24 months), a single-subject brain with median brain size and relatively straight medial longitudinal fissure will be used as a single-subject template for inter-subject registration and manual labeling. All neural structures will be delineated in axial images with high contrast from DTI and the anatomical information from DTI tractography, followed by adjustment in coronal and sagittal images.^47,48^ Graphic metrics will also be computed. Primary brain connectome outcome measures will include global graph measures, including cost and global efficiency, and local/regional graph measures, including local efficiency and clustering coefficient.

##### Resting-state functional connectivity MRI analysis

Resting-state functional connectivity MRI will be used to noninvasively assess brain function by simultaneously probing multiple brain networks using the contrast induced by differences in blood oxygenation. Resting-state data will be preprocessed using previously validated techniques that minimize the influence of noise (i.e., head motion, physiologic noise, and scanner noise) on measured blood oxygen-level-dependent (BOLD) signals.^49^ To assess functional connectivity, we will use seed-based correlation methods and graph theoretic techniques. A priori cortical, subcortical, and cerebellar regions of interest (ROIs) will be defined using automatic anatomic labels optimized for neonates and very young children.^50^ These ROIs will be defined in T1/T2 anatomical images and registered to Echo-planar imaging data. A study-specific template will be created for the entire cohort and functional images will be normalized to this template. BOLD time series measured from each ROI will be correlated (i.e., Pearson correlation) to signals obtained from other regions. Changes in connectivity strength and connectivity patterns over time will be measured. To complement this approach, we will also use graph theoretic techniques.

#### Statistical analysis plan

For neuroimaging outcomes (Aim 1), linear and generalized linear mixed-effect regression models will be fit using data from the MRI scans at 0–1, 6, and 24 months to compare trajectories of brain development measures (e.g., cortical and deep cerebral gray matter volumes) over time in infants with and without opioid exposure, controlling for study site and child and family characteristics. The test of a time-by-exposure status interaction will allow us to determine if trajectories over time differ between exposed and unexposed infants. The model will be selected based on the type of outcome with linear models for normally distributed continuous outcomes and generalized linear models for categorical or non-normally distributed continuous outcomes. In addition to the comparisons by the dichotomous opioid exposure variable (i.e., exposed versus unexposed), similar models will examine the impact of the level of opioid exposure on neuroimaging outcomes.

For neurodevelopmental and behavioral outcomes (Aim 2), linear mixed-effect models will be used for continuous outcomes (e.g., Bayley scores) and generalized linear mixed-effect models for categorical outcomes (e.g., presence of a diagnosis), accounting for study site and infant and family characteristics. These models allow us to statistically account for clustering of subjects within study sites. In addition, for outcomes where measurement error is likely to occur, such as different domains of behavioral assessments, latent variable approaches (i.e., structural equation modeling) will allow us to combine more than one measure into a single underlying latent variable to reduce measurement error in models. These models permit testing of hypotheses that, compared with unexposed controls, children with opioid exposure are more likely to have low cognitive scores, demonstrate increased motor abnormalities, and have more behavioral problems, controlling for other possible contributing factors (e.g., other antenatal exposures, postnatal environment, demographics). Sensitivity analyses will be conducted to examine the impact of including subjects with other antenatal exposures in the models.

For Aim 3, possible moderators (e.g., family and home factors) of antenatal opioid exposure effects on outcomes will be evaluated as shown in Fig. 2. Using the mixed-effect and SEM models described above, we will test for interactions between opioid exposure and potential moderators/confounders to determine whether opioid exposure has a differential impact on infant outcomes for some subgroups compared to others. For example, we can test whether antenatal opioid exposure effect is amplified among infants who also have a poor home environment.

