## Introduction

Neonatal opioid withdrawal syndrome (NOWS) has emerged as a generational byproduct of the opioid epidemic. Following the increase in opioid use by pregnant mothers,^1,2^ the incidence of NOWS has also continued to increase with recent prevalence estimates observing growth from 4.0/1000 births in 2010 to 7.3/1000 births in 2017.^3^

The effects of maternal opioid use on the fetal brain are largely unknown. Basic science studies indicate multiple negative effects of in utero opioid exposure on brain development, including decreased neurotransmitter levels, decreased neurogenesis, increased apoptosis, and altered myelination.^4–6^ Human imaging studies suggest that children exposed to opioids in utero have smaller regional brain volumes^7–9^ and altered structural connectivity as compared with unexposed children.^7,8,10,11^ Functional connectivity also appears to be altered in infants with prenatal exposure to opioids and other drugs.^12–14^ However, previous magnetic resonance imaging (MRI) studies on the brain development of opioid-exposed infants and children have been small and may not have used appropriate control groups. It is therefore unknown whether these potential effects seen in the brains of opioid-exposed children are related to opioids themselves or to other confounding factors such as polysubstance use, nicotine exposure, maternal mental health disorders, or environmental factors, such as poverty.

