## Methods

### Study aims and hypotheses

The OBOE Study will address three specific aims. The first aim is to determine the impact of antenatal opioid exposure on brain structure and connectivity over the first 2 years of life. We hypothesize that antenatal opioid exposure reduces cortical and deep cerebral gray matter volumes and disrupts the structural and functional connectome as measured by diffusion tensor imaging (DTI) and resting-state functional connectivity MRI over the first 2 years of life. The second aim is to define medical, developmental, and behavioral outcomes over the first 2 years of life in infants exposed to opioids. Our hypothesis is that the magnitude of antenatal opioid exposure and co-exposures with other psychotropic drugs will independently affect developmental and behavioral outcomes. The third aim is to explore whether and how the home environment, maternal mental health, and parenting modify trajectories of brain connectivity and neurodevelopment over the first 2 years of life. For this aim, we hypothesize that several identifiable and modifiable postnatal factors mediate the effect of antenatal opioid exposure and jointly contribute to poorer neurodevelopmental outcomes.

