Aspects of the child–caregiver relationship and environment will be assessed via caregiver report and observation. Caregivers will complete the Maternal Postnatal Attachment Questionnaire (MPAQ)^41^ to measure the quality of interactions in the domains bonding, absence of hostility, and pleasure in interaction during the 6-month visit. During the in-home 12-month visit, examiners will complete the *Home Observation for Measurement of the Environment* (HOME).^42^ The HOME^42^ is a comprehensive assessment of nurturance and stimulation in the home environment based on observation and caregiver interview. Should a home visit not be feasible or if the parents refuse the home visit, a version of the HOME assessment which has modified for administration virtually through a video visit will be used.

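### Aim 2 tests the opioid effect adjusted for the postnatal environment, which Aim 3 hypothesises to be a mediator, and no Aim 2 analysis is described that gives the total effect

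*Protocol article*

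**What the plan says.** In the Statistical analysis plan section of the Protocol article, the Aim 2 models serve to test whether "children with opioid exposure are more likely to have low cognitive scores, demonstrate increased motor abnormalities, and have more behavioral problems" than unexposed controls, "controlling for other possible contributing factors (e.g., other antenatal exposures, postnatal environment, demographics"). The only Aim 2 sensitivity analysis described concerns subjects with other antenatal exposures.

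The article gives the postnatal factors several roles:

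- **Mediator.** The Aim 3 hypothesis (Study aims and hypotheses) is that "several identifiable and modifiable postnatal factors mediate the effect of antenatal opioid exposure and jointly contribute to poorer neurodevelopmental outcomes".
- **Modifier.** The Aim 3 statement in the same section is to "explore whether and how the home environment, maternal mental health, and parenting modify trajectories of brain connectivity and neurodevelopment". Table 1 lists the family and home measures under a heading for effect modifiers.
- **Moderator or confounder.** The Aim 3 analysis says "we will test for interactions between opioid exposure and potential moderators/confounders".
- **Confounder.** The Introduction speaks of "other confounding factors such as polysubstance use, nicotine exposure, maternal mental health disorders, or environmental factors, such as poverty".

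The Aim 2 hypothesis itself is that "the magnitude of antenatal opioid exposure and co-exposures with other psychotropic drugs will independently affect developmental and behavioral outcomes". It does not say whether the effect is total or net of the home.

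**The concern.** The home, attachment and parenting-stress measures are taken after the exposure. Table 1 places attachment at 6 months, HOME at 12 months ("During the in-home 12-month visit, examiners will complete the" instrument, per Psychosocial assessments) and parenting stress at 6, 18 and 24 months. The Bayley-4 is given at 24 months. A 12-month home score cannot cause an antenatal exposure. It can lie on the path from exposure to outcome, as Aim 3 supposes, or stand in for background disadvantage that affects both.

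If it lies on the path, adjusting for it takes the mediated part out of the exposure coefficient. What remains is a direct effect at best, and then only if no unmeasured cause is shared by the home environment and the outcome.

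Interpretation is at stake. The Discussion (Role of parenting and the home environment) notes that in several earlier studies exposure effects lost significance after control for social and home variables. If the only Aim 2 model repeats that control, a null result could mean no effect, or an effect that runs through the home.

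**Working it through.** **1. What the described analyses deliver.** Aim 2 names the postnatal environment as a covariate class. Its sensitivity analysis varies something else. Aim 3 tests interactions, which address modification and yield no indirect effect. Structural equation models are mentioned for combining measures into latent variables and for the same interaction tests, with no mediated path described. So the total effect is not the stated target of any Aim 2 analysis, and the Aim 3 mediation hypothesis has no matching analysis.

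**2. The stated power.** Inputs from Sample size and power estimates: 200 exposed and 100 unexposed, 80% follow-up at 24 months (160 and 80), d = 0.5, two-sided alpha 0.01.

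- SE = sqrt(1/160 + 1/80) = 0.1369
- Power = Φ(d/SE − 2.576) = Φ(3.651 − 2.576) = 85.9%; the noncentral t with 238 df gives 85.3%

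The stated 85% reproduces.

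**3. Power for the adjusted coefficient under assumed mediation.** The mediated share m is not in the documents and is an assumption. The coefficient targeted is 0.5 × (1 − m), with residual SD held at 1.

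| m (assumed) | Coefficient | Coefficient/SE | Power |
|---|---|---|---|
| 0% | 0.50 | 3.651 | 86% |
| 20% | 0.40 | 2.921 | 64% |
| 40% | 0.30 | 2.191 | 35% |
| 60% | 0.20 | 1.461 | 13% |

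Two refinements act in opposite directions. Correlation between exposure and mediator lowers power: with R² = 0.1, the 40% row falls to 31%. A mediator that predicts the outcome shrinks the residual variance and raises power. Suppose it explains 20% of within-group variance. An indirect effect of 0.2 then implies paths of 0.447 × 0.447. With exposure variance 2/9, the variance inflation is 1 + 0.2 × 2/9 = 1.044, SE = 0.1369 × sqrt(0.8 × 1.044) = 0.125, and power at 40% mediated is Φ(0.30/0.125 − 2.576), about 43%.

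**4. Is the shift always towards zero?** A large linear simulation (400,000 children, outcome coded so that higher is worse, all coefficients assumed) gives these exposure coefficients:

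| Structure | True total | Without postnatal variable | With it |
|---|---|---|---|
| Mediator, same direction (0.3 direct + 0.5 × 0.4) | 0.50 | 0.50 | 0.30 |
| Same, plus a background confounder that is adjusted for | 0.50 | 0.50 (0.76 if confounder ignored) | 0.30 |
| Proxy for a background confounder only | 0.30 | 0.42 (0.30 if confounder adjusted) | 0.30 |
| Mediator, opposite direction (0.5 direct − 0.5 × 0.4) | 0.30 | 0.30 | 0.50 |
| Mediator, unmeasured common cause, same sign | 0.50 | 0.51 | 0.17 |
| Mediator, unmeasured common cause, opposite sign | 0.50 | 0.50 | 0.49 |

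In the last two rows the direct effect is 0.30, so the adjusted value recovers neither a direct effect nor, except by coincidence, the total. Rows two and three show that adjusting for the background confounder itself recovers the total effect without the postnatal variable.

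**The case against.** A reader might infer that the Aim 2 estimate is certainly over-adjusted and biased towards no effect. The documents do not support that, for these reasons.

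- Mediation is stated once, as a hypothesis of an exploratory aim. Elsewhere the same factors are modifiers, moderators or confounders. If they are proxies for background disadvantage, adjustment removes bias.
- An opposite-direction mediator, or unmeasured causes shared by environment and outcome, can move the estimate either way.
- A direct effect may be intended. Aim 2 speaks of independent effects, and the Introduction asks whether findings reflect opioids themselves or confounding that includes environmental factors.
- The covariates are an illustrative list. The article does not call this the primary model or say that HOME, attachment or parenting stress enter it. Exact covariates normally belong in an analysis plan, and the conceptual-framework figure could not be read here.

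All of this stands against certainty about direction and size. It does not remove the inconsistency. The article itself names the postnatal environment as a covariate class and itself hypothesises mediation. The independence wording concerns opioid magnitude and psychotropic co-exposures and does not mention the home. The confounder role can largely be served by background measures collected at 0–1 month: socioeconomic status, maternal IQ and maternal medical and psychiatric history. The moderator role calls for interaction terms, which Aim 3 already has.

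Nor is the stated 85% wrong. It is correct for a 0.5 SD difference. The point is that it does not carry over to a coefficient with a smaller target.

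**Conclusion.** The point holds as an inconsistency in the causal role given to the postnatal environment, together with an Aim 2 estimand that is not stated. As described, Aim 2 conditions on factors that Aim 3 expects to carry part of the effect, and neither a model without them nor a mediation analysis is described.

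If mediation runs towards poorer outcomes, as the article hypothesises, the adjusted coefficient understates the total effect. On the assumptions of a 0.5 SD total effect, mediated shares of 20% to 60% and residual SD of 1, power for it would be about 64% down to 13%, against the planned 85%. These figures are illustrative, because the documents supply no mediated share and do not fix the direction of the shift. This is an inexpensive improvement that makes a null result interpretable. It does not show that the planned estimate is biased.

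**What to change.** 1. State the Aim 2 primary estimand as the total effect of antenatal opioid exposure. Adjust for site and for background factors that precede birth or are fixed around it: demographics, socioeconomic status at 0–1 month, maternal education and IQ, maternal mental health history and other antenatal exposures. Some of these are recorded after birth; treating them as background is an assumption to state.
2. Report the model that adds postnatal factors (for example HOME, attachment, parenting stress) separately, labelled as a direct-effect or mediation analysis under Aim 3, with its assumption of no unmeasured common causes of environment and outcome.
3. Reconcile the mediation hypothesis with the wording on modifiers, moderators and confounders. Either describe a mediation analysis or reword the hypothesis.

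The cost is wording and one more model per outcome, with no new data. The drawback is some residual confounding in the primary model if the baseline measures capture background disadvantage imperfectly. Showing both models makes that visible. The background adjustment must stay: simply dropping the postnatal variables without it would leave confounding in place, as the 0.76 against a true 0.50 in the simulation shows.

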**Fig. 2 Fig2:**
[figure not shown]
Conceptual Framework of the ACT NOW OBOE Study. Conceptual framework of the relationships between exposures, effect modifiers, and outcomes.

Missing data are possible for any longitudinal study and are a special cause of concern for the population to be enrolled in this study. We will closely monitor attrition and conduct logistic regression models to compare the characteristics (e.g., opioid exposure, site, maternal and family characteristics) of subjects who remain in the study at 2 years versus those who dropped out to determine if data are missing at random. Patterns of item-level missing data will be examined to determine if particular types of questions (e.g., questions related to maternal drug use) have greater levels of missing data or have missing data rates that differ across groups, suggesting that they may not be reliable. The impact of missing data of both types will be minimized through use of appropriate likelihood-based estimators.^51–53^ These methods yield unbiased estimates and accurate standard errors without sacrificing cases (and thus maximizing statistical power) when data are missing completely at random or predicted by other variables in a given model but independent of the potential values of the outcome itself (i.e., missing at random). If subjects do not appear to be missing at random, we will use pattern mixture models to account for the informative attrition.^54^

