##### Neuroimaging

Infants will undergo an MRI scan at three time points during study participation (0–1, 6-, and 24-month time points), with each site using a 3 T MRI scanner. The “feed and swaddle” technique will be used to optimize natural sleep and eliminate the need for sedation. This technique includes infants being fed immediately before the exam, undressed to a diaper, swaddled in a blanket and MedVac bag (CFI Medical Solutions, Fenton, MI), and positioned in the scanner. Ear plugs and Minimuffs (Natus Medical Incorporated, San Carlos, CA) will be applied for hearing protection. For the 6- and 24-month scans, previously published^28^ methods will be used, including (1) scheduling scans in the evening hours around the infant’s bedtime or during naptime for the 6-month-olds; (2) skipping daytime naps the day of the scheduled imaging session; (3) allowing time for the family to get the infant to sleep in a private testing room outside the MRI suite and then waiting for 15–20 min before moving the infant to the scanner; (4) reducing acoustic noise levels by using earplugs, Minimuffs, headphones, and sound-insulating foam inserts in the scanner; (5) using a larger MedVac immobilization bag for the toddlers and securing after the child falls asleep; and (6) designing the MRI protocol to require <30 min to ensure uninterrupted sleep during the scan. Research staff will be in visual contact with infants throughout the MRI exam. Total MRI scan time for each time point should be approximately 60 min. MRI protocols are provided in Table 2.

**Table 2 Tab2:** MRI specifications by sequence and type of scanner.

Component	Siemens (Prisma)				Philips (Ingenia)			
	T1	T2	Diffusion	fMRI	T1	T2	Diffusion	fMRI
TR (ms)	1600	3200	3440	1000	9.5	2500	2329	1000
TE (ms)	3.01	492	98.4	30	4.5	252	102	30
TI (ms)	1000	N/A	N/A	N/A	1000	N/A	N/A	N/A
Resolution (mm)	1 × 1 × 1	1 × 1 × 1	2.5 × 2.5 × 2.5	3 × 3 × 3	1 × 1 × 1	1 × 1 × 1	2.5 × 2.5 × 2.5	3 × 3 × 3
Flip angle (deg)	15	T2 Var	78	80	8	90	90	80
Parallel imaging	2×	2×	Off	Off	2×	2×	Off	Off
MultiBand acceleration	Off	Off	3	4	Off	Off	3	4
Diffusion directions	N/A	N/A	48	N/A	N/A	N/A	48	N/A
*b*-values	N/A	N/A	1000	N/A	N/A	N/A	1000	N/A
Acquisition time	3:26	2:45	3:10	7:01	3:20	3:05	2.10	7:01

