#### Sample size and power estimates

Given the paucity of definitive studies on effects of antenatal opioid exposure to 2 years, power calculations reflect a scientifically meaningful effect size of half a standard deviation unit for a longitudinal outcome based on a sample size of 300 (200 exposed infants and 100 unexposed infants). We assumed three repeated measures (0–1, 6, 24 months), with 80% follow-up at 24 months, a conservative intra-cluster correlation of 0.5 for repeated measures, and a two-sided test with a conservative Type 1 error of 0.01 in recognition of the multiple aims specified for our analysis.

With a sample size of 300, the study will have statistical power of 99% to detect effects this size (*d* = 0.5) with statistical significance. A smaller effect size of a third of a standard deviation (*d* = 0.33) is still detectable with 98% power. Power will be lower but respectable to detect meaningful differences in binary outcomes. Using the proportion of head circumference below the 10th percentile as an example, under the same assumptions, shows that for a control group proportion of 10%, there is 82% power to detect proportions in excess of 25% in the opioid-exposed group (relative risk of 2.5 or higher).

The cross-sectional analyses have lower but still respectable power, especially for continuous outcomes such as the 24-month Bayley cognitive score. As before, for a scientifically meaningful effect size of half a standard deviation unit, based on the sample size of 300 with 80% follow-up at 24 months, a conservative two-sided test at Type I error of 0.01 has 85% power to detect effects of this size with statistical significance. Not surprisingly, only large effects of antenatal opioid exposure (relative risk of 3.7 or higher) are detectable for binary outcomes with low (5%) prevalence in the control/unexposed infants.

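### The missing-at-random check compares infants retained at 2 years with dropouts, so it does not examine scans lost among retained infants, which is a missing-data process specific to Aim 1

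*Protocol article*

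**What the plan says.** All places are in the Protocol article.

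- **Statistical analysis plan, missing-data paragraph (after the Fig. 2 caption).** Logistic regression will compare the characteristics of "subjects who remain in the study at 2 years versus those who dropped out to determine if data are missing at random". The second type is item-level: "Patterns of item-level missing data will be examined to determine if particular types of questions" are more often left blank, or are left blank at different rates across groups. The default handling is then given: "The impact of missing data of both types will be minimized through use of appropriate likelihood-based estimators". The paragraph states that these estimators need data missing completely at random, or missingness predicted by other variables in the model and independent of the outcome's own value. The fallback is: "If subjects do not appear to be missing at random, we will use pattern mixture models to account for the informative attrition".
- **Statistical analysis plan, Aim 1.** Mixed-effect "models will be fit using data from the MRI scans at 0–1, 6, and 24 months", controlling for site and for child and family characteristics that are not listed.
- **Neuroimaging.** The feed-and-swaddle "technique will be used to optimize natural sleep and eliminate the need for sedation". For the 6- and 24-month scans the measures include "designing the MRI protocol to require <30 min to ensure uninterrupted sleep during the scan".
- **Sample size and power estimates.** 200 exposed and 100 unexposed infants, with 80% follow-up at 24 months. This is the only loss mentioned.

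**The concern.** Retention in the study and possession of a brain outcome are different things here. An infant may attend at 24 months, complete the Bayley and the BITSEA, and yet not fall asleep in the scanner, wake before the functional run, or move too much for the images to be used. Another may miss the 6-month scan and come back later. The attrition model codes both as remaining, and neither is an unanswered question. The Neuroimaging section's own precautions (evening or nap-time scheduling, skipped naps, a wait after sleep onset) show that sleep is a recognised threat to obtaining a scan.

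Scan loss may also be related to what is being studied. The plan hypothesises more behavioural problems in exposed children, and arousal or poor sleep could plausibly affect whether a scan succeeds. If so, the attrition check could report good and balanced retention while usable scans differ by group and by behaviour, and nothing in the stated plan would bring that to light.

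**Working it through.** **1. Where each kind of loss falls in the stated plan**

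| Infant | Attrition model | Item-level check | Pattern-mixture trigger |
|---|---|---|---|
| Leaves before 2 years | dropped out | no | yes |
| Skips a questionnaire item | remains | yes | no |
| Attends at 24 months, no usable scan | remains | no | no |
| Misses the 6-month scan, returns | remains | no | no |

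The last two rows are losses of Aim 1 data that no stated check examines.

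**2. What the mixed model does with them.** A missing scan contributes no record at that visit; it is not treated as observed. Likelihood estimation remains valid if, given the model's covariates and the infant's other scans, the loss does not depend on the unseen value. Differences in scan success by exposure group or site are therefore covered. Dependence on behaviour or sleep that is not in the model, but is related to the brain outcome, is not. The article does not say whether NNNS-II, BISQ or BITSEA enter the MRI models; Table 1 lists them as child outcomes.

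**3. Reproducing the plan's own figure.** Inputs from Sample size and power estimates: d = 0.5, two-sided alpha 0.01 (z = 2.576), 80% of 100 and 200 = 80 and 160.

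Power = Φ(d / √(1/n₀ + 1/n₁) − 2.576). √(1/80 + 1/160) = 0.1369; 0.5/0.1369 = 3.651; Φ(3.651 − 2.576) = 85.9% (85.3% with the noncentral t). The stated 85% reproduces when every retained infant has the measurement. The plan illustrates it with the Bayley, which needs no scan.

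**4. Number affected.** Retained: 300 × 0.8 = 240; dropped out: 60. Let s be the share of retained infants with a usable 24-month scan. The article does not give s, so these values are assumptions. Retained without a scan = 240 × (1 − s).

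| s (assumed) | Usable 24-month scans | Retained, no scan | Relative to 60 dropouts |
|---|---|---|---|
| 0.8 | 192 | 48 | 0.8 |
| 0.75 | 180 | 60 | 1.0 |
| 0.5 | 120 | 120 | 2.0 |

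**5. Precision.** For the longitudinal average exposure effect that matches the design, I used generalised least squares with three visits, correlation 0.5, d = 0.5, alpha 0.01, assumed visit completeness of 100%, 90% and 80%, and s applied at every visit:

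| s (assumed) | Power, longitudinal average effect |
|---|---|
| 1.0 | 99.0% |
| 0.8 | 98.2% |
| 0.6 | 95.9% |
| 0.5 | 93.2% |

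A contrast of the 24-month scan alone, by the formula in step 3, would have 75.5% power at s = 0.8 (64 vs 128) and 50.2% at s = 0.5 (40 vs 80), but the article does not plan that contrast for Aim 1. The time-by-exposure interaction was not computed.

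**The case against.** The best reply is that this is a journal article. Image-quality rules and scan-level missingness normally belong in the imaging manual or the full analysis plan, a completer-versus-dropout comparison is an ordinary check, and nothing says it is the only one. That stands as far as detail goes: an unseen plan may already cover scan loss. It does not remove the point. The article states a specific rule, enumerates two types of missing data, and ties the fallback to attrition. For Aim 1 that rule uses the wrong unit.

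It is also fair that the mixed model does not discard or misread infants with a missing scan, and that an infant who skips the 6-month scan is an ordinary intermittent gap for such a model. That stands too, under missing at random. The weakness is that the assumption is not checked for scans.

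A reader might infer more than the document supports:

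- **That scan failure is the main source of missing brain data.** No success rate is given, and scan failure exceeds the planned dropout only if success among retained infants is below 75%.
- **That retained infants without a scan are analysed as complete.** This is true of the diagnostic only, not of the outcome model.
- **That the bias runs towards no effect.** The mechanism is plausible, but its direction is conjecture.
- **That Aim 1 is badly underpowered as a result.** The low figures belong to a single-visit contrast; power for the longitudinal average effect stays above 90% across the assumed range.

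**Conclusion.** The point holds as a mismatch between the missing-data check and the Aim 1 outcomes. The diagnostic, the two named types and the pattern-mixture trigger all work at the level of subject dropout or questionnaire items, so scan loss among retained infants goes unexamined in the stated plan. The risk is undetected bias rather than lost power. Its size and direction cannot be derived from the article. The illustrative 48 to 120 infants rests on the stated 80% retention and on an assumed 50% to 80% scan success at 24 months. The change should be made; the text does not show that Aim 1 is invalid without it.

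**What to change.** For Aim 1, define a usable-scan indicator (yes/no) for each visit and modality: structural, diffusion and functional.

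- **Diagnostic.** Fit the planned logistic models to each indicator, with exposure, site, and maternal and family characteristics. Add only the behavioural measures and earlier scan results available by that visit. By Table 1, NNNS-II comes from 0–1 month, while BISQ is given only at 12 months and BITSEA at 12 and 24, so the 12-month BISQ and BITSEA can serve the 24-month scan only. No earlier scan exists at 0–1 month.
- **Sensitivity analysis.** Bring predictors of scan loss into the MRI models as auxiliary variables, through a joint model, multiple imputation or inverse-probability weights. Extend the pattern-mixture analysis from dropout to scan-missingness patterns.
- **Reporting.** Give usable-scan rates by group and visit.

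The existing dropout comparison can stay alongside. The cost is revised wording and modest extra analysis. The behavioural and family measures are already scheduled, image usability has to be judged for the analysis anyway, and no new data collection is needed.
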